**Fig. 1 Fig1:**
[figure not shown]
The mediating and moderating role of variables in the effect of feedback on treatment outcome (path c)

## Methods

### Study design

This study is a partially randomized controlled trial. Clients will be randomly assigned to one of two groups. An additional intervention group (IG 1) will be generated from an existing archival data set via propensity score matching.Control group (CG): Treatment with continuous assessments but without computer based feedback to therapists.Intervention group 1 (IG1): Patients in this group received treatment with continuous assessments including computer-based feedback to therapists after each session. This group is a matched sample.Intervention group 2 (IG2): Treatment with continuous assessments including computer based prediction as well as feedback/adaptation tools to therapists after each session including an alarm for NOT patients.

The project was submitted to and approved by the Ethics Committee of the University of Trier. Since it is a non-invasive procedure, patients are informed about data protection law consequences and their opportunity to refuse to accept the storage and use of video data for research purposes at any time. An explanation of the various experimental conditions will be given at the end of the project.

### Setting

The patient samples will be assessed at the research outpatient clinic at the University of Trier. Treatments are conducted by cognitive-behavioral therapists in training with different levels of experience. In the outpatient clinic standardized ways of recording and documenting treatment data is established. Session reports are assessed via touch screen data entry devices, whereas pre- and post as well as 5-session assessment are entered by research assistants. The infrastructure has been further improved for this study. Computerized status and progress feedback is provided via a secured website (feedback portal).

### Inclusion and exclusion criteria

The sample will include all patients who enter psychotherapy during the recruitment period and fulfill the following inclusion criteria:At least one anxiety or depressive disorder (ICD-10: F32, F33, F40, F41, F42, F43)At least 3 treatment sessions

The exclusion criteria are:Organic, including symptomatic mental disorders (ICD-10: F00-F09)Mental and behavioral disorders due to psychoactive substances (ICD-10: F10-F19)Schizophrenia, schizotypal, and delusional disorders (ICD-10: F20-F29)Acute suicidality

### Randomization

First, patients will be randomly assigned to therapists after the SCID-I interview which will be conducted by an independent trainee (see Fig. 2). Second, patients will be randomized to one of two groups (CG or IG2). This means that the same therapist treats patients who are in the CG as well as patients who are in the IG2. The assignment procedure of patients to therapists will secure, that each therapist will treat at least eight patients and that each therapist has patients in both conditions. As an additional randomization condition a matching procedure is applied, which ensures that the therapists do not differ in terms of their level of clinical experience and years of using the feedback system in IGs and the CG. A second intervention group (IG1) is generated via propensity score matching from already existing archival data set based on diagnoses, intake severity as well as social-demographic variables like age and gender.

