Three moderators and two mediators of the feedback effect will be investigated in hypotheses 3 and 4 (see also Fig. 1): Moderators: therapists’ attitudes towards feedback, feedback usage and diagnoses; Mediators: Therapists’ awareness for negative developments and treatment length. In order to control for therapist effects, therapists will be modelled as random effects at level two.

Therefore, *Optimal Design Software for Multilevel and Longitudinal Research* (Version 3.01; [50]) was used to determine the minimal effect that can be detected with sufficient power, given the sample size calculation above. Assuming a therapist effect of 5% and k = 50 therapists delivering the treatments to j = 8 patients each, a small effect (d = .2) can be detected with sufficient power (1-β = .8). Thus, given the sample size calculated for the primary hypotheses, the secondary analyses can be conducted with sufficient power using multi-level models (e.g., [51]). Ensuring the stability of the results, all analyses will be checked with Mplus software (e.g., [52]).

Additional Monte Carlo simulations with Mplus (Version 7; [52]) were run to specifically test the mediation models from hypotheses 3 and 4. Assuming again small effects for the direct associations, 10,000 datasets have been simulated with the actual sample size of the study sample. These simulations revealed a sufficient power of 1-β = .874. Thus, given the sample size calculated for the primary hypotheses, the mediation analyses can also be conducted with sufficient statistical power to detect indirect mediation effects adjusting for above described control variables.

Furthermore, the analyses will be controlled for the following potential influencing factors: comorbidity (number of additional diagnoses, additional personality disorders), initial impairment, clinical experience as well as experience with the feedback system.

Finally, the data of the project will have a hierarchical data structure because patients will be nested within therapists. Two-level hierarchical models will be applied to the data to correct for therapist influences [51].

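### The therapist balance claimed for both intervention groups and the control group cannot be ensured for archival IG1, the group used in both main hypotheses

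*Protocol article*

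**What the plan says.** All of the following is in the protocol article.

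- **Randomization, therapist balance.** As part of the randomization there is a matching step, "which ensures that the therapists do not differ in terms of their level of clinical experience and years of using the feedback system". The statement goes on to cover "years of using the feedback system in IGs and the CG". The plural takes in IG1 as well as IG2.
- **Randomization, who is randomized.** Patients are randomized between CG and IG2 only, so that "the same therapist treats patients who are in the CG as well as patients who are in the IG2". Each therapist is to have at least eight patients and some in each of these two conditions.
- **Randomization, source of IG1.** IG1 comes by propensity score matching from an "archival data set based on diagnoses, intake severity as well as social-demographic variables like age and gender".
- **Objectives.** H1 compares IG1 with CG and H2 compares IG2 with IG1, in each case among not-on-track (NOT) patients.
- **Sample size calculation and data analyses.** Therapists are random effects at level two. The control variables include "clinical experience as well as experience with the feedback system".
- **Assessments.** Therapist data such as clinical experience are collected in the clinic's basic documentation.
- **Setting.** "The infrastructure has been further improved for this study".

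**The concern.** A condition attached to randomization can shape only allocations still to be made. IG1 patients had their therapists before the trial began, so the condition cannot reach them. What could balance therapists for IG1 is the propensity score, and no therapist variable is named there.

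At stake are both main hypotheses, since each has IG1 on one side. The only randomized contrast, IG2 vs CG, is not a main hypothesis. If IG1 therapists had a different level of experience or a different number of years with the feedback system, that difference would enter H1 and H2 together with the effect of feedback or of the support tools. A reader who relies on the stated assurance would think this had been excluded by design.

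**Working it through.** **Step 1. The text, group by group.**

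| | CG | IG2 | IG1 |
|---|---|---|---|
| Randomized | yes | yes | no, archival |
| Therapists shared by design | with IG2 | with CG | not stated |
| Variables balanced by matching | therapist experience, years with system | same | diagnoses, intake severity, socio-demographic |
| Covered by the assurance | yes | yes | yes |
| Procedure can deliver it | yes | yes | no |

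The last two rows conflict for IG1 only. The illustrative wording about age and gender leaves open which socio-demographic variables are used. It does not naturally extend to therapist characteristics.

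**Step 2. What the analysis adds.** On a generous reading, the control variables and random effects apply to H1 and H2 as well as to the moderator and mediator models. Both quantities named in the assurance are then covariates, and therapist identity is in the model. A random effect accounts for clustering. Where IG1 therapists are not trial therapists, it does not remove a systematic difference between the two sets. No term for calendar period is listed.

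**Step 3. The plan's own figure, and how sensitive the tests are.** The point disputes no figure. The plan's 108 NOT patients for H2 reproduce:

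- f = .30/2 = .15, correlation .4, two assessments
- λ = f² × N × 2/(1 − .4) = .0225 × 108 × 2/.6 = 8.1
- power from the noncentral F(1, 106) = .805

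This calculation assumes that IG1 differs from the other group only through the intervention. To show what an uncorrected difference would do, let δ be an *assumed* shift, in outcome SDs, in the difference between groups in mean pre-post change. The documents give no value for δ.

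- SD of change = √(2 × (1 − .4)) = 1.095
- H2, 54 vs 54: SE = 1.095 × √(1/54 + 1/54) = 0.211
- H1, 54 vs 27: SE = 1.095 × √(1/54 + 1/27) = 0.258
- noncentrality = δ/SE, two-sided α = .05

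| Assumed δ | H2 rejection rate, no true effect | H1 rejection rate, no true effect | H2 power if δ runs against IG2 |
|---|---|---|---|
| 0 | 5% | 5% | 80.5% |
| 0.1 | 7.6% | 6.7% | 65% |
| 0.2 | 15.6% | 11.9% | 47% |
| 0.3 | 29.2% | 20.9% | 29% |

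On this scale the effect behind the plan's 108 is √8.1 × 0.211 = 0.60, so δ must not be read as a fraction of .30. The table takes no account of the planned covariates and is a scale, not an estimate. A shift that favours IG1 helps H1 and hurts H2; the opposite shift does the reverse.

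**The case against.** Several counter-arguments have force.

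- **The non-randomized status of IG1 is disclosed.** The article calls the trial partially randomized and describes the archival matching openly. A condensed article may also leave the full list of propensity variables to another document. That stands as far as missing detail goes. It does not answer a positive statement that balance is ensured for a group the procedure cannot reach.
- **The analysis adjusts for the same two quantities and models therapists.** This is real mitigation, provided the data exist for archival therapists. It happens in the analysis, however, and leaves calendar period out.
- **The matching step has a use of its own.** A reader might think it redundant for CG vs IG2 because each therapist treats both. That does not follow. The article requires patients in both conditions but fixes no ratio within a therapist: seven IG2 patients and one CG patient would comply. The mix of therapist experience can therefore differ between CG and IG2, and the step is worth keeping there.
- **Actual differences are not documented.** A reader might infer that therapists and era do differ in H1 and H2, that the shift favours IG2, or that it is a stated share of the assumed d = .30. The article supports none of these. It gives no archival dates, therapist roster or rate of drift. IG1 comes from an existing archive, and therapist overlap is possible. Therapists are trainees at varying levels, so an earlier cohort need not be less experienced. The remark on improved infrastructure follows a description of data entry and does not show a change in outcomes.

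**Conclusion.** The point holds as a mismatch between a stated design property and the procedure described. The assurance of equal therapist experience and equal years with the system is not delivered for IG1, and IG1 is in both main contrasts. The planned covariates and therapist random effects partly mitigate this; calendar period remains unaddressed.

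No bias has been demonstrated, and its size and sign are unknown. The rejection rates above depend wholly on the assumed shift and on no adjustment being made. The conclusion itself needs only two readings: that the plural covers IG1, and that the listed propensity variables include no therapist characteristic. It should be corrected, but it does not by itself invalidate the comparisons.

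**What to change.** 1. In Randomization, limit the therapist-balance assurance to CG vs IG2.
2. Add to the IG1 propensity model the therapist's clinical experience and, where recorded, years using the feedback system, both as of the patient's first session.
3. Report standardised differences on these variables for IG1 vs CG and for IG1 vs IG2.
4. State that H1 and H2 are non-randomized comparisons in which period differences cannot be excluded.
5. As a sensitivity analysis, restrict to therapists who treated both archival and trial cases.

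Treatment start date should not go into the propensity model. Archival and trial dates may not overlap, in which case the score would separate the groups completely and leave nothing to match. Within-therapist matching is better kept to the sensitivity analysis, because a continuing therapist had fewer years with the system when treating the archival cases, so the two matching aims conflict.

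**Cost.** Clinical experience is already collected; years with the system for archival cases may not be. The matching is desk work. The price is somewhat looser matches or an IG1 smaller than the planned 169.

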**Fig. 2 Fig2:**
[figure not shown]
Diagram of patient flow within the study

### Assessments

Table 1 gives an overview of the instruments as well as their time of measurement within the project.

**Table 1 Tab1:** Diagnostic instruments and assessment schedule

	Begin	Every session	Every 5th session	End
SCID-Interview [29] (SCID)	x			
Brief Symptom Inventory [33] (BSI)	x			x
Outcome Questionnaire [53] (OQ-30)	x		x	x
11-item Short version of Hopkins‘Symptomchecklist [31] (HSCL-11)		x		
Assessment for Signal Clients [5] (ASC)	x		x	
Affective Style Questionnaire [54] (ASQ)	x		x	
Patient Health Questionnaire [55] (PHQ-9)	x		x	
Generalized Anxiety Disorder [56] (GAD-7)	x		x	
Global Assessment of Functioning [41] (GAF)	x	x		x

In addition to psychometric instruments, socio-demographic and psychosocial data of both patient and therapist (e.g. clinical experience) are collected as part of the basic documentation system in the outpatient center. Axis I diagnoses are assessed with the SCID-I [29] and Axis II disorders are assessed with the IDCL-P checklist [30]. Both assessment procedures are part of the already existing routine within the outpatient center.

### Assessment of outcome instruments

#### Hopkins symptom checklist – short form (HSCL-11)

The HSCL-11 is an 11-item self-report inventory for the assessment of symptomatic distress [31]. It was developed based on the HSCL-25, which is a brief version of the Hopkins Symptom Checklist-90 [32]. In the present study, the HSCL-11 will be administered at the beginning of each session. The items are responded to on a 4-point Likert scale ranging from 1 (“not at all”) to 4 (“extremely”). The mean of the 11 items represents the patient’s level of global symptomatic distress, it is highly correlated with the GSI (*r* = 0.91) and also has high internal consistency (α = .92; [31]).

#### Brief symptom inventory (BSI)

Symptom severity will be measured pre- and post treatment using the BSI ([33]; German translation of [34]) which is a 53-item self-report inventory inquiring about physical and psychological symptoms within the last week. It is the brief form of the Derogatis’ Symptom Check-List-90 Revised (SCL-90-R; [34]), which assesses 9 subscales with the following dimensions: somatization, obsessive-compulsive, interpersonal sensitivity, depression, anxiety, hostility, phobic anxiety, paranoid ideation, and psychoticism. Item response takes place on a 5-point Likert scale ranging from 0 (“not at all”) to 4 (“extremely”). Psychometric properties for this index can be regarded as excellent (αpre = .96; αpost = .97).

#### Outcome questionnaire-30 (OQ-30)

The OQ-30 will be administered pre-; each 5 sessions and post-treatment. This 30 items self-report measure is designed to assess patient outcomes during the course of therapy. The OQ has three primary dimensions: (a) subjective discomfort, (b) interpersonal relationships, and (c) social role performance. All 30 items can be aggregated to create a total score. The OQ-30 is a short from of the OQ-45 comprising the 30 items that are most sensitive to client change and demonstrated high levels of congruence with the OQ-45 in measurement of patient outcome [35–37]. The OQ-30 showed an adequate internal consistency in our sample (α = .90). For an enhanced comparability the OQ-30 will be applied because it is internationally the most widely used instrument in feedback studies [12].

As part of the feedback and adaptation tools (see below), the ASC and ASQ are assessed every fifth session. To be able to compare the results of this project to feedback studies conducted in the UK [38] the GAD-7 and PHQ-9 will be used as symptom specific instruments every fifth session.

### Assessment of feedback related variables

To examine the usage of the feedback system, user statistics for each therapist will be recorded [39, 40]. These access statistics of the feedback system will allow to evaluate the frequency of feedback use as well as the amount of time spend within the feedback system and for each specific case.

Therapists’ attitudes towards feedback will be assessed as soon as each therapist starts working within the project. In order to evaluate the modifications therapists make due to feedback (Fig. 1, path b), therapists will be asked ten specific questions after the termination of each treatment.^1^ For control purposes therapists in the control group will also be asked whether they used additional questionnaires or some material from the clinical support tools even though this material was not available for this patient (but for a different patient of this therapist).

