**Methods/design:**

The research project investigates in a randomized controlled trial the effectiveness as well as moderating and mediating factors of psychometric feedback to therapists. In the intended study a total of 423 patients, who applied for a cognitive-behavioral therapy at the psychotherapy clinic of the University Trier and suffer from a depressive and/or an anxiety disorder (SCID interviews), will be included. The patients will be randomly assigned either to one therapist as well as to one of two intervention groups (CG, IG2). An additional intervention group (IG1) will be generated from an existing archival data set via propensity score matching. Patients of the control group (CG; *n* = 85) will be monitored concerning psychological impairment but therapists will not be provided with any feedback about the patients assessments. In both intervention groups (IG1: *n* = 169; IG2: *n* = 169) the therapists are provided with feedback about the patients self-evaluation in a computerized feedback portal. Therapists of the IG2 will additionally be provided with clinical support tools, which will be developed in this project, on the basis of existing systems. Therapists will also be provided with a personalized treatment recommendation based on similar patients (Nearest Neighbors) at the beginning of treatment. Besides the general effectiveness of feedback and the clinical support tools for negatively developing patients, further mediating and moderating variables on this feedback effect should be examined: treatment length, frequency of feedback use, therapist effects, therapist’s experience, attitude towards feedback as well as congruence of therapist’s and patient’s evaluation concerning the progress. Additional procedures will be implemented to assess treatment adherence as well as the reliability of diagnosis and to include it into the analyses.

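### Therapist attitude (H3, H3b) is scheduled at project entry, but IG1 was treated earlier: for 40% of patients the moderator is missing or post-treatment unless the archive holds it, and the stated power ignores this

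*Protocol article*

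**What the plan says.** Three statements in the Protocol article bear on this point.

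- **When attitude is measured.** Assessment of feedback related variables: therapists' "attitudes towards feedback will be assessed as soon as each therapist starts working within the project". No other time point is given. Objectives makes attitude a moderator in H3 and relates it to therapists' awareness of negative change in H3b.
- **Where IG1 comes from.** Study design: "Patients in this group received treatment with continuous assessments including computer-based feedback to therapists after each session. This group is a matched sample". Randomization: "A second intervention group (IG1) is generated via propensity score matching from already existing archival data set", with matching "based on diagnoses, intake severity as well as social-demographic variables like age and gender". Attitude is not among the matching variables named.
- **What power is claimed.** Sample size calculation and data analyses names attitude, usage and diagnoses as moderators, and awareness and treatment length as mediators. It states that 50 therapists with 8 patients each allow a small effect (d = .2) to be detected with power .8. For the mediation models of H3 and H4 it reports power .874, where "10,000 datasets have been simulated with the actual sample size of the study sample". Neither figure excludes IG1, and the abstract counts IG1 in the planned total of 423.

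A related item is the set of questions on changes made because of feedback (Fig. 1, path b): "therapists will be asked ten specific questions after the termination of each treatment".

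**The concern.** A moderator should be fixed before the outcome it is meant to modify. For CG and IG2, a score taken when the therapist enters the project comes before the treatment of that therapist's study patients. For an archival group it cannot. A therapist who treated IG1 patients and never joined the project has no score. One who did join is scored after those treatments, when the attitude may already reflect whether feedback seemed to help.

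H3 asks what moderates the effect of feedback, and the feedback-only effect in this plan is IG1 versus CG. In that contrast the whole feedback arm would have a late or absent score and the whole control arm an early one. Timing is then confounded with arm, and moderation cannot be separated from an influence of outcome on attitude. A model pooling all three groups would mix the two kinds of score. The stated power would also credit the analysis with patients who cannot supply the variable.

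**Working it through.** **Step 1: reproduce the plan's sample size.** Inputs from Sample size calculation and data analyses: 108 not-on-track (NOT) patients for IG1 and IG2 together (54 each), 27 for CG, a NOT rate of 40%, and 25% added for drop-out.

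- IG1 and IG2: 54 / 0.40 = 135 each. CG: 27 / 0.40 = 67.5, taken as 68. Total 338.
- Times 1.25: 135 × 1.25 = 168.75, taken as 169 each; 68 × 1.25 = 85. Total 169 + 169 + 85 = 423.

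This matches Table 2.

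**Step 2: share affected.**

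- All planned patients: 169 / 423 = 0.3995, or 40%.
- NOT patients at target: 54 / (27 + 54 + 54) = 54 / 135 = 40%.
- NOT patients in the IG1 versus CG contrast: 54 of 81, which is the entire feedback arm of that contrast.

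**Step 3: timing by group on the stated schedule.**

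| Group | Patients | Treatment | Attitude score |
|---|---|---|---|
| CG | 85 | in the project | at project entry, before treatment |
| IG2 | 169 | in the project | at project entry, before treatment |
| IG1 | 169 | already given | absent, or after treatment, unless archived |

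**Step 4: power for the secondary analyses.** The plan's input is 50 × 8 = 400 patients. Prospective patients number 85 + 169 = 254. At least 400 − 254 = 146 of the 400 must therefore be archival.

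Taking d = .2 at 400 at face value, and assuming that the detectable effect scales with 1/√N at unchanged patients per therapist and allocation ratio, the value at 254 is 0.2 × √(400/254) = 0.25.

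An indicative check uses a normal approximation for a two-group contrast within therapists, with 1:1 allocation, the plan's therapist effect of 5% and no covariates: detectable d = 2.80 × √(4 × 0.95 / N).

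- N = 400: detectable d = .27; power for d = .2 is .54.
- N = 254: detectable d = .34; power for d = .2 is .37.

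This check does not reproduce the plan's d = .2. The article does not give the design option behind that figure, so only the relative loss should be read from it (.34 / .27 = 1.26, against √(400/254) = 1.25). Both calculations concern a main contrast in all patients. Moderation among NOT patients is a cross-level interaction in about 81 patients at target (27 CG + 54 IG2) and needs its own simulation.

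**Step 5: the .874.** It is reported for the mediation models. The article does not list the simulation inputs, so whether attitude was one of them cannot be told.

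**The case against.** The strongest reply is that the article does not describe the archive. The clinic already had a feedback system, and therapists' years of using it are evidently known, so attitude may have been recorded when the IG1 patients were treated. This stands: the point has to be conditional. It does not remove the point, because the only stated measurement is at project entry and the power is claimed without any such condition.

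Second, project therapists may also enter with past feedback experience, so their entry attitude can reflect earlier results as well. This is fair. But their score still precedes the outcomes of their study patients, which is not so in IG1.

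Third, the section on implementing the feedback tools describes IG1 in the present and future tense, as if therapists were still to treat it. The abstract, Study design and Randomization all make it archival, so that wording does not rescue the timing.

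Several stronger readings are tempting but not supported:

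- *The path-b questions are measured after the outcome in IG1.* They follow the end of treatment in every group by design, and they are not among the listed moderators and mediators. For IG1 the issue is only absence or late recall, which is secondary.
- *H4 falls with H3.* Its mediators are the congruence of session-wise GAF and HSCL ratings, and the number of sessions. Neither is shown to be missing in IG1.
- *The .874 is wrong as a whole.* It needs restating only for models that include attitude.
- *The loss can be expressed as a detectable correlation across therapists.* The same therapist treats CG and IG2 patients, so the H3 test is cross-level. It is also unclear whether the minimum of eight patients per therapist includes archival ones, so no reliable therapist count follows.

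**Conclusion.** The concern holds for one moderator, therapist attitude, in H3 and H3b. On the schedule as written, 169 of 423 patients (40%) have no attitude score that precedes their treatment, and in IG1 versus CG the timing of the score is confounded with arm. The stated power rests on 400 patients where the described design delivers 254 with a valid score. On the plan's own figure, scaled by 1/√N, the detectable effect rises from d = .20 to about .25.

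This assumes that IG1 is wholly archival and that the archive holds no attitude scores from the time of treatment. The article says the first and is silent on the second. H1 and H2 are untouched, so the consequence is limited to secondary hypotheses. It is still worth correcting, because an attitude effect could otherwise be reported as adequately powered moderation when the timing does not allow that reading.

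**What to change.** 1. State whether the archive holds therapist attitude scores, and when they were taken.
2. Include IG1 in the attitude analyses (the attitude part of H3, and H3b) only where a score was recorded before that patient's treatment.
3. Otherwise restrict these analyses to the randomised CG and IG2 patients, restate the power for that sample (254 patients, about 81 NOT at target) and label them exploratory.
4. Restate the .874 only for models that include attitude.
5. As a secondary matter, say whether answers to the path-b questions exist for IG1 or would have to be recalled late.

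The cost is wording and a rerun of the power calculations, with no new data. There are two downsides. The stated power becomes less favourable. And CG versus IG2 tests moderation of feedback plus tools, not of feedback alone, which the plan should say openly.
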